#### Main research hypotheses

We will evaluate group differences in the number of psychosocial issues discussed during the genetic counseling sessions using analysis of (co)variance. We will assess counselors’ awareness of their counselees’ psychosocial problems by calculating the agreement between counselees’ and counselors’ on their ratings, per domain, of the psychosocial problems experienced by the counselees. We will calculate an Intraclass Correlation Coefficient (ICC2.1.A
[34]) per domain for both the intervention and control group. Group differences will be assessed by treating the ICC’s as Pearson correlation coefficients and using Fisher’s r-to-z transformation to test for statistical differences per domain. Analysis of (co)variance will also be used to evaluate group differences in referral to additional information sources and/or referral to psychosocial care services, and the actual use of such services.

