### Timing and content of study measures

Counselees will be asked to complete questionnaires at: (1) baseline, prior to randomization; (2) approximately 4 weeks following the first genetic counseling session, before the final counseling session takes place; and (3) approximately 4 months after the telephone-based counseling session.

The counselors will be asked to complete a baseline questionnaire at the start of the study, a checklist at the end of each counseling session, and a final questionnaire at the end of the study. Both the in-person and the telephone-based genetic counseling sessions will be audiotaped by two independent raters ([name]) for purposes of content analysis (see below). Inter-rater reliability will be assessed by double coding 10% of the audiotaped sessions, equally divided between the intervention group and control group sessions.

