### Sample size and power calculations

We have based the sample size estimates on expected differences between the intervention group and the control group in communication between the genetic counselors and counselees about psychosocial issues. Overall power calculations for estimating sample size requirements were based on the following criteria for defining a substantively meaningful statistical association: (1) power of 0.80, (2) alpha of 0.05, and an (3) effect size “d” of 0.4. With these criteria, 99 cases per study arm are needed, resulting in a total sample size of 198 cases.

We anticipate that approximately 25% of the counselees will not have more than one counseling session and thus will not have a DNA-test disclosure session. Therefore, in order to have sufficient power in the second phase of the trial, we will include 264 participants at the start of the trial.

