#### Comparability of intervention and control group

The comparability of the intervention and control groups at baseline will first be evaluated in terms of sociodemographic and clinical characteristics. Student’s t-test or appropriate non-parametric tests will be used. If, despite the stratified randomization procedures, the groups are found to be statistically different on one or more baseline characteristics, these variables will be adjusted for in subsequent analyses.

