#### Secondary research hypotheses

We will employ analysis of (co)variance to evaluate group differences in the frequency of with which the genetic counselor initiated the discussion of psychosocial issues. Analysis of (co)variance will also be used to evaluate group differences in the amount of counseling time spent discussing psychosocial issues, and the total length of the counseling session. To evaluate group differences in cancer worries and general distress, we will use analysis of covariance, with the previous scores on these questionnaires as covariate. Logistic regression analysis will be used to evaluate differences between groups in the prevalence of cancer genetics-specific problems. Group differences in satisfaction with the genetic counseling process will be examined with Student’s t-tests and chi square tests, where appropriate. Intervention group and counselor satisfaction with the intervention will be reported descriptively.

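### A free gain in precision is left unclaimed: baseline HADS and Cancer Worry scores are not prespecified as covariates for the primary count of issues discussed, whose covariates depend on baseline significance tests

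*Protocol article*

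**What the plan says.** Counselees complete a questionnaire at "baseline, prior to randomization". Table 1 lists its content as cancer worries, general distress and demographic data. Under Recruitment and randomization, allocation follows only once that questionnaire has been returned completed, so in principle every randomized counselee has both scores.

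The sample size rests on "expected differences between the intervention group and the control group in communication between the genetic counselors and counselees about psychosocial issues". The count of issues discussed is the first primary hypothesis, and Main research hypotheses gives its model: "We will evaluate group differences in the number of psychosocial issues discussed during the genetic counseling sessions using analysis of (co)variance". No covariate is named and none is excluded.

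Two other places deal with covariates:

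- Comparability of intervention and control group: the arms "will first be evaluated in terms of sociodemographic and clinical characteristics". Baseline characteristics that turn out statistically different are then adjusted for in later analyses.
- Secondary research hypotheses: for cancer worries and general distress, "we will use analysis of covariance, with the previous scores on these questionnaires as covariate".

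Recruitment and randomization describes minimization within counselor on gender and cancer syndrome. The analysis sections do not say that these factors enter any model.

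**The concern.** The secondary scales have a fixed covariate. The outcome that sizes the trial does not. Its covariate set is left to a significance test between randomized arms. Under randomization, a significant baseline difference is a chance event. Whether a variable is flagged says nothing about whether it predicts the number of issues discussed. A strongly prognostic variable that happens to be balanced would be left out, and a useless one that happens to be imbalanced would go in. The primary model also comes to depend on the data.

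HADS and CWS are the natural candidates. The count is coded against the 26 PAHC items, whose domains include general emotional and cancer-specific issues. Table 1 places no other psychosocial score before randomization. If they predict the count, fixed adjustment narrows the interval and takes any chance imbalance in baseline distress or worry out of the primary contrast. What is at stake is precision and prespecification. The randomized comparison is not biased by leaving the scores out.

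**Working it through.** **Inputs from Sample size and power calculations.** "1) power of 0.80, (2) alpha of 0.05"; standardized effect d = 0.4; "99 cases per study arm are needed, resulting in a total sample size of 198 cases"; 25% without a disclosure session; 264 enrolled. Sidedness is not stated.

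**Reproducing the plan's figure.** The normal-approximation formula is n per arm = 2(z₀.₉₇₅ + z₀.₈₀)²/d² = 2(1.960 + 0.842)²/0.16 ≈ 98.1, rounded up to 99. The t-based solution is 99.08, with power 0.7997 at 99 per arm. A one-sided test would need only 78, so the plan is two-sided. The inflation is 198/0.75 = 264. All three stated figures reproduce without any covariate.

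**Effect of adjustment.** Let R be the multiple correlation of baseline HADS and CWS with the count. ANCOVA multiplies the residual variance by (1 − R²). With n per arm, the noncentrality is λ = [0.4/√(1 − R²)]·√(n/2). It is tested two-sided at 0.05 on 2n − 2 − 2 degrees of freedom, the last 2 being for the two scores. The article gives no R, so 0.1 to 0.5 is an assumed range.

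As an example, take n = 99 and R = 0.3: λ = (0.4/√0.91)·√49.5 = 2.950 on 194 df, giving power 0.835. Unadjusted, λ = 0.4·√49.5 = 2.814 on 196 df, giving 0.800.

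| R (assumed) | 1 − R² | Interval width relative to unadjusted, √(1 − R²) | Power, 99 per arm (phase II) | Power, 132 per arm (phase I) | Unadjusted n per arm equivalent to 99, i.e. 99/(1 − R²) |
|---|---|---|---|---|---|
| unadjusted | 1 | 1 | 0.800 | 0.899 | 99 |
| 0.1 | 0.99 | 0.995 | 0.804 | 0.902 | 100 |
| 0.2 | 0.96 | 0.980 | 0.815 | 0.911 | 103 |
| 0.3 | 0.91 | 0.954 | 0.835 | 0.924 | 109 |
| 0.4 | 0.84 | 0.917 | 0.863 | 0.942 | 118 |
| 0.5 | 0.75 | 0.866 | 0.899 | 0.962 | 132 |

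The 132 per arm is 264/2, all participants at the first session. The 99 is 132 × 0.75.

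**Where the gain could be used.** Because 264 × 0.75 = 198 exactly, the inflation covers only counselees without a disclosure session. It leaves nothing for withdrawal, a missed call or an unusable tape. If phase II ended with 90 analysable sessions per arm (an illustration, not a figure from the article), power would be 0.761 unadjusted and 0.799 with R = 0.3.

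**The case against.** A reader might infer that the plan analyses the count without HADS and CWS and so throws away power. The text does not support this. It allows analysis of covariance and excludes no covariate. The trigger in the comparability section refers to baseline characteristics in general, which could take in HADS or CWS if they were imbalanced. This part of the objection stands: the accurate statement is that the scores are not prespecified, not that they are left out.

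A journal article may also leave a covariate list to the full protocol or analysis plan. That would answer a complaint of mere silence. It does not answer this point fully, because the article does state a rule for covariates in later analyses, and that rule is the weaker method.

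The size of the gain is assumed. The article gives neither R nor the spread of the count, and it offers reasons to doubt a high R. The outcome is what is discussed and not what is felt. The Background says counselors concentrate on biomedical information, and the Abstract says problems often go undetected. Baseline distress might therefore predict discussion only weakly, at least among controls. In phase II the scores are more distant still, since the call comes about four weeks after the DNA result. In phase I, where they are closest in time, power is already about 0.90. All of this stands and limits the claim.

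Nor does the article's own warning about low prevalence help the case. That concerns mainly how much there is to find, which covariate adjustment does not change. Extending the same two covariates to the referral and service-use outcomes is likewise unsupported: nothing here was calculated for them, and referral is coded as whether it happened.

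**Conclusion.** The point holds as a free improvement and not as an error. Two plausible prognostic scores are available before randomization, and the article commits to neither for the primary count. The rule it does state picks covariates by chance imbalance. Fixed adjustment is the better method.

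The stated sample size stands, and the 80% power needs no covariate. The gain at 99 per arm runs from 0.4 points of power (R = 0.1) to 9.9 points (R = 0.5). At 132 per arm it runs from 0.3 to 6.3 points. At R of 0.2 or less it is negligible, and at 0.3 modest. These figures assume d = 0.4 before adjustment, a two-sided 0.05 test, and a linear relation with the same residual variance in both arms. The value of R is undocumented. The case for prespecifying does not depend on R being large, because a fixed covariate set also keeps the primary model independent of the observed data.

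**What to change.** In Main research hypotheses, state that the number of issues discussed is analysed by ANCOVA with baseline HADS total and baseline CWS score as covariates, together with the minimization factors (counselor, gender and cancer syndrome), whatever the observed baseline balance. For this outcome, let that sentence replace the significance-triggered rule in the comparability section. A descriptive baseline table can remain.

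The cost is one or two sentences, two degrees of freedom for the two scores, and no new data. The minimization factors use further degrees of freedom. Their number depends on how many counselors and syndrome categories there are, which the article does not give. The sample size needs no change.

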## Abstract

**Background:**

Individuals with a personal or family history of cancer, can opt for genetic counseling and DNA-testing. Approximately 25% of these individuals experience clinically relevant levels of psychosocial distress, depression and/or anxiety after counseling. These problems are frequently left undetected by genetic counselors. The aim of this study is to evaluate the efficacy of a cancer genetics-specific screening questionnaire for psychosocial problems, the ‘Psychosocial Aspects of Hereditary Cancer (PAHC) questionnaire’ together with the Distress Thermometer, in: (1) facilitating personalized counselor-counselee communication; (2) increasing counselors’ awareness of their counselees’ psychosocial problems; and (3) facilitating the management of psychosocial problems during and after genetic counseling.

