The aim of this randomized, controlled trial is to evaluate the efficacy of the PAHC questionnaire when used routinely in daily clinical cancer genetics practice in: (1) facilitating communication during genetic counseling sessions about relevant psychosocial issues; (2) increasing genetic counselors’ awareness of the psychosocial problems of their counselees; and (3) facilitating the appropriate management of these cancer genetic-specific psychosocial problems. Specifically, our primary research hypotheses are that the use of the PAHC questionnaire during genetic counseling will:

(1) increase significantly the number of psychosocial issues discussed during genetic counseling sessions;

(2) increase significantly the genetic counselors’ awareness of the psychosocial problems experienced by their counselees; and

(3) improve significantly the management of cancer genetic-specific psychosocial problems as evidenced by the referrals to psychosocial care and/or to sources of information about psychosocial issues. Additionally, we hypothesize that the routine use of the PAHC questionnaire will:

(4) increase significantly the number of discussed issues initiated by the counselor;

(5) increase significantly counselees’ satisfaction with the counseling process;

(6) decrease significantly counselees’ levels of cancer worry and distress during and after the genetic counseling process;

(7) decrease significantly the cancer genetic-specific problems experienced by the counselee after the genetic counseling process; and

(8) *not* increase significantly the total duration of the genetic counseling session.

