#### Counselors’ awareness

Counselors’ awareness of the psychosocial problems as experienced by their counselees will be assessed with a checklist completed by the counselors directly after the counseling sessions. The counselor will be asked to report whether (s)he believes that the counselee is experiencing problems in each of the 6 problem domains covered by the PAHC questionnaire on a 4-point scale ranging from (1, “no problem” to 4, “a severe problem”). The counselors’ ratings will be compared to the responses provided by the counselees on the PAHC questionnaire.

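### The agreement coefficient used for counselor awareness cannot by itself show that more problems are recognised; recognition and false alarms should be estimated alongside it

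*Protocol article*

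**What the plan says.** Primary hypothesis 2 (Background) is that use of the questionnaire will "increase significantly the genetic counselors’ awareness of the psychosocial problems experienced by their counselees". The deficit that motivates it is given in the Abstract: "These problems are frequently left undetected by genetic counselors". The Discussion likewise speaks of problems going undetected and of improving their recognition.

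Under Counselors' awareness, the measurement is a checklist filled in after each session: "The counselor will be asked to report whether (s)he believes that the counselee is experiencing problems in each of the 6 problem domains", on a 4-point scale from no problem to severe problem. Then: "The counselors’ ratings will be compared to the responses provided by the counselees on the PAHC questionnaire".

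Under Main research hypotheses, the analysis is "We will assess counselors’ awareness of their counselees’ psychosocial problems by calculating the agreement between counselees’ and counselors’ on their ratings". The coefficient follows: "We will calculate an Intraclass Correlation Coefficient (ICC2.1.A" and so on, per domain in each arm. The arms are compared by treating the ICCs as correlations and "using Fisher’s r-to-z transformation to test for statistical differences per domain". No other awareness analysis is stated. In particular, there is none of the share of problem domains that the counselor recognises, and none of the direction of disagreement.

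Two other passages matter. Intervention group procedure already defines a problem domain: it is printed red when at least one item is answered in either of the top two categories, and green otherwise. Comparability of intervention and control group says that, where baseline characteristics differ, "these variables will be adjusted for in subsequent analyses".

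**The concern.** The claim of interest is one-directional: counselors should notice more of the problems that counselees have. The ICC is two-directional. It is unchanged if the two raters are swapped, so an unnoticed problem and a wrongly suspected one both lower it, and shared ratings of no problem raise it.

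The intervention can act on both sides, because the printout marks domains without a problem (green) as well as those with one (red). An arm difference in the ICC could therefore come from better recognition, from fewer false alarms, or from both, and the coefficient does not say which. At stake is the reading of a primary result. A positive ICC comparison could be reported as better detection when detection did not change, and a null one as no improvement when detection rose.

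**Working it through.** **Sample size.** The article states 99 per arm for d = 0.4, alpha 0.05 and power 0.80. With two-sided alpha, 2 × ((1.960 + 0.842)/0.4)² = 98.1, so 99 reproduces. 198/0.75 = 264 also reproduces. That gives 132 per arm in phase I and about 99 in phase II. The calculation is based on the communication outcome; the article gives no power figure for awareness.

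**Inputs that the documents do not give (assumptions).** Share of domain ratings at problem level p = 25% (range 10–50%); recognition s = 45% at baseline; false alarms f = 20% at baseline. The article's own 25% is the share of counselees with clinically relevant distress or similar problems, not a rate per domain.

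**Formula, two-category version.** The share rated as a problem by the counselor is q = p·s + (1−p)·f. Then

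ICC = (p·s − p·q) / [ (p(1−p) + q(1−q))/2 + (p−q)²/2 ].

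The comparison is z = (atanh ICC₁ − atanh ICC₀)/√(2/(n−3)), two-sided 0.05.

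**Baseline.** q = 0.1125 + 0.15 = 0.2625. Numerator 0.1125 − 0.0656 = 0.0469. Denominator (0.1875 + 0.1936)/2 + 0.0125²/2 = 0.1906. ICC = 0.246.

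**Scenario A worked through (recognition stays 45%, false alarms fall to 5%).** q = 0.1125 + 0.0375 = 0.15. Numerator 0.1125 − 0.0375 = 0.075. Denominator (0.1875 + 0.1275)/2 + 0.1²/2 = 0.1625. ICC = 0.462. At n = 132, z = (0.499 − 0.251)/0.1245 = 1.99.

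| Scenario (from 45% / 20%) | Recognition | False alarms | ICC | Chance of favourable significance per domain, n = 132 (n = 99) |
|---|---|---|---|---|
| A: fewer false alarms only | 45% | 5% | 0.25 → 0.46 | 51% (40%) |
| B: better recognition only | 65% | 20% | 0.25 → 0.42 | 34% (26%) |
| C: better recognition, more over-calling | 65% | 35% | 0.25 → 0.24 | 2% (2%) |
| D: both improve | 65% | 10% | 0.25 → 0.56 | 86% (75%) |

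**Range over p = 10% to 50%, n = 132.** Scenario A runs from 63% down to 27%. Scenario C never exceeds about 6%.

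**4-point ratings.** Simulation at the same rates, with the analysis-of-variance form of the ICC and 132 per arm, gives lower coefficients because severity within each class also disagrees. The pattern is the same:
- A: ICC 0.19 → 0.33, 26% favourable per domain.
- B: ICC 0.18 → 0.32, 23%.
- C: ICC 0.18 → 0.19, 3%.

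No gain in recognition (A) and a 20-point gain (B) are close to indistinguishable on this scale.

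**Other starting values, 99 per arm, p = 25%.** Recognition fixed at 50% with false alarms falling from 30% to 5% gives ICC 0.18 → 0.51 and a 76% chance of significance. Recognition rising from 50% to 75% with false alarms rising from 5% to 20% gives 0.51 → 0.49 and about 2%.

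**Why a direct measure should be pooled.** In a single domain with about 25 problem cases per arm (99 × 0.25), a recognition gain from 50% to 75% has only about 44% power. Pooled over six domains with clustering allowed for, a gain from 45% to 65% had 95% power in simulation at 132 per arm and 87% at 99.

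**The case against.** The strongest reply is that agreement is how this protocol chooses to define awareness. A counselor who correctly sees that a domain is not a problem knows the counselee better, and the green coding shows that this too is wanted. On that reading scenario A is a real success. This stands in part: the ICC is a legitimate measure of overall accuracy. It is not a measure of recognition, which is what the rationale speaks of.

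The ICC also works in the most natural case. Counselors who hold a colour-coded printout would be expected to improve on both sides (scenario D), and the ICC then rises clearly. Being an absolute-agreement coefficient, it also penalises systematic under-rating by counselors. A and C each require them to use the printout unevenly.

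A reader might go further and infer that recognition should replace agreement as the deciding test. The documents do not support that. Counselors are unblinded and complete the checklist themselves, so a recognition-only test can be passed by over-calling. In scenario C correct classification falls from 0.25 × 45% + 0.75 × 80% = 71% to 0.25 × 65% + 0.75 × 65% = 65%, and true problems among flagged domains fall from 43% (0.1125/0.2625) to 38% (0.1625/0.425). A flat ICC is defensible there.

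Two further inferences also fail. One is that shrinking problems by the telephone session would depress the intervention ICC: hypothesis 7 concerns problems after the counseling process, and does not state a reduction before that call. The other is that the analysis breaks a promise of adjustment: that promise is conditional on baseline differences being found.

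**Conclusion.** The point holds as a limit on interpretation. Hypothesis 2 is framed around problems experienced and left undetected, and the only stated analysis mixes recognition with false alarms. A significant ICC difference therefore does not establish greater recognition, and a null one does not exclude it.

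The direction of this conclusion follows from the symmetry of the coefficient and needs no assumed rate. Its size does: prevalence, recognition and false-alarm rates are all assumptions, and the effect in scenario A weakens as problems become more common.

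It does not follow that the ICC is invalid or that hypothesis 2 cannot be tested. The sample size is unaffected. This is a worthwhile, inexpensive addition to the analysis, not a defect that invalidates the trial.

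**What to change.** Keep the per-domain ICCs and add one pre-specified pooled analysis: a logistic mixed or GEE model over the six domains, clustered on counselee, with counselor as a factor and any covariates that the baseline-comparability rule brings in. From it, estimate by arm:

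- recognition: the counselor rates a problem in domains that are red under the rule in Intervention group procedure;
- false alarms: the counselor rates a problem in domains that are green under that rule.

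State in advance the level of the counselor's 4-point rating that counts as a problem; the article gives none. State also that improved recognition will be concluded only if the recognition estimate rises and the false-alarm result is reported with it, and not from the ICC alone.

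Cost: analysis wording and slightly more analysis work. Both sets of ratings are already planned for both arms. The counselor's rating is dichotomised in this added model, which loses some severity information; the retained ICCs still use the full scale.

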The results of the PAHC questionnaire + DT will be printed and attached to the counselee’s medical record so that they are available to the genetic counselor prior to the relevant counseling session (face-to-face in phase I and telephone-based in phase II). To facilitate the genetic counselor’s rapid review of the questionnaire output, all problem domains for which the counselee responds “quite a bit” or “very much” to at least one item are color coded *red*, indicating a problem area that should preferably be discussed during the counseling session. All other problem domains, are color coded *green*, indicating that there is, in principle, no need to discuss it during the counseling. Additionally, based on the literature and analysis of a validation of the DT in a previous study by our group using a heterogeneous sample of counselees for cancer in the Netherlands, a score of 4 or greater on the DT is used to indicate a clinically relevant level of distress
[25,29]. Finally, the counselor will receive information about whether the counselee is interested in obtaining additional professional psychosocial support for any given problem area. Scores on the DT above the cut-off point, and counselees’ requests for additional psychosocial support are also color coded *red.* Additionally, to increase the ease of interpretation of the results, all items above the threshold will be printed in a bold font, and those items that are not above the threshold will be printed in light-grey. All counselors will receive written instructions/guidelines and training in the use of the PAHC questionnaire and the DT.

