### Control group procedure

Counselees in the control group will complete the PAHC questionnaire and DT as described above for the intervention group. However, the results of these questionnaires will not be provided to the genetic counselors.

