### Primary outcome measures

The primary outcomes of the trial are: (1) discussion of psychosocial problems; (2) counselors’ awareness of the counselees’ psychosocial problems; and (3) management of psychosocial problems during and after genetic counseling.

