#### Management of psychosocial problems

The audiotapes of the counseling sessions will also be used to evaluate how the counselees’ psychosocial problems are managed. Specifically, the study-specific checklist will be used to code whether counselees were referred to additional sources of information about how to deal with psychosocial problems (e.g., websites or written materials) or to additional psychosocial counseling. The counselees will be asked to report their actual use of psychosocial services.

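### Management is compared as any referral in any counselee, so the primary analysis cannot show whether extra referrals reach the people who reported a problem

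*Protocol article*

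**What the plan says.** In the Protocol article, the Background states the third aim as "facilitating the appropriate management of these cancer genetic-specific psychosocial problems". The matching hypothesis is that the questionnaire will "improve significantly the management of cancer genetic-specific psychosocial problems as evidenced by the referrals to psychosocial care" or to information sources. Primary outcome measures lists the outcome as "3) management of psychosocial problems during and after genetic counseling".

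Management of psychosocial problems says how it is measured from the audiotapes: "the study-specific checklist will be used to code whether counselees were referred to additional sources of information" or to further psychosocial counseling. Actual use of services is self-reported. Under Main research hypotheses the analysis is: "Analysis of (co)variance will also be used to evaluate group differences in referral to additional information sources and/or referral to psychosocial care services", and likewise for actual use of services.

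Need is recorded before the session. In the intervention arm, "all problem domains for which the counselee responds “quite a bit” or “very much” to at least one item are color coded" red. A Distress Thermometer (DT) score of 4 or more marks clinically relevant distress, and requests for support are flagged too. For the other arm, "Counselees in the control group will complete the PAHC questionnaire and DT as described above for the intervention group". Study sample sets no entry criterion based on having a problem.

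For another yes/no outcome, Secondary research hypotheses says: "Logistic regression analysis will be used to evaluate differences between groups in the prevalence of cancer genetics-specific problems".

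**The concern.** The aim concerns problems that counselees have and whether they are managed appropriately. The analysed quantity is whether a referral was made, to anyone. Nothing in the article links a referral to a red domain, a raised DT score or a request for support.

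Two things follow. A rise in referrals among people who reported no problem counts towards success just as a rise among people who did. And because having a problem is not required for entry, a gain confined to those with need is averaged over everyone else and becomes harder to detect. A primary conclusion of improved management could therefore rest on a difference that does not speak to the aim, or be missed when the aim is met.

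A lesser point is the model. Referral coded as whether it happened is yes/no, and it is analysed by analysis of (co)variance, whereas problem prevalence gets logistic regression.

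**Working it through.** **1. The plan's own sample size.** Inputs from Sample size and power calculations: d = 0.4, alpha 0.05 (taken as two-sided), power 0.80, 25% without a disclosure session.
- n per arm = 2 × (1.960 + 0.842)² / 0.4² = 98.1, rounded up to 99; total 198.
- 198 / (1 − 0.25) = 264, that is 132 per arm.

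The figures reproduce. They rest on communication, not on management, so this point does not touch them.

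**2. Does the model matter for the test?** I compared the ANOVA F test on 0/1 data with the Pearson chi-square test in every possible 2×2 table.
- 99 per arm: 0 of 10,000 tables give a different decision at 0.05. Type I error is 0.039 to 0.052 for true rates of 2% to 40%.
- 132 per arm: 0 of 17,689 tables differ. Type I error is 0.045 to 0.052.
- With covariates, a simulated ANCOVA with 3% or 9% referral by covariate stratum gave about 4.8% type I error and 95% coverage.

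**3. Can untargeted referral produce a significant result?** The article gives no referral rates, so these are assumptions: need share q; 40% of those with need referred in both arms (no benefit to them); 5% of the others referred in control and x in the intervention arm.
- Control rate p_C = 0.40q + 0.05(1 − q).
- Intervention rate p_I = 0.40q + x(1 − q).
- Power = Φ[(|p_I − p_C| − 1.96·se₀)/se₁], with se₀ from the pooled rate and se₁ from the two separate rates (normal approximation).

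Example with q = 0.25, x = 0.20, 132 per arm:
- p_C = 0.10 + 0.0375 = 0.1375; p_I = 0.10 + 0.15 = 0.25; difference 0.1125; pooled rate 0.19375.
- se₀ = √(0.19375 × 0.80625 × 2/132) = 0.0487.
- se₁ = √((0.1375 × 0.8625 + 0.25 × 0.75)/132) = 0.0482.
- Power = Φ[(0.1125 − 0.0954)/0.0482] = Φ(0.356) = 0.64.

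| Need share | x = 15% | x = 20% | x = 25% |
|---|---|---|---|
| 25% | 0.36 | 0.64 | 0.85 |
| 50% | 0.15 | 0.28 | 0.44 |

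Each entry is the chance of a significant all-comer result with no gain for anyone in need.

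**4. How much is a targeted gain diluted?** Let referral rise from 40% to 60% only among those with need, and stay at 5% among the others.
- q = 0.25: the overall difference is 0.25 × 0.20 = 0.05 (13.75% to 18.75%). All-comer power is 0.195. Among those with need (0.25 × 132 = 33 per arm) it is 0.37.
- q = 0.50: the overall difference is 0.10 (22.5% to 32.5%). All-comer power is 0.44. Among those with need (66 per arm) it is 0.63.

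**5. Precision of a by-need estimate.** With 33 per arm and rates of 40% and 60%, the 95% half-width is 1.96 × √((0.24 + 0.24)/33) = 0.24, that is, 24 percentage points.

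**The case against.** The strongest reply is that the analysis matches the hypothesis as written: improvement is to be judged by referrals, and referrals are what is compared. Randomization balances need in expectation, so the comparison is unbiased for any referral. Both statements stand. What remains is a gap between that quantity and the aim, which speaks of appropriate management.

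The scenario in step 3 also runs against the design of the tool, which marks domains without problems green and tells counselors there is in principle no need to discuss them. That is fair: the scenario shows what the analysis cannot detect, not what is likely. The 25% share is also borrowed. In the article it is clinically relevant distress, depression or anxiety after counseling. A single item at the upper two response levels turns a domain red before the session, so the share with need on that definition could be much larger. At 50% the probabilities fall by about half, as the table shows.

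A reader might infer that analysis of (co)variance invalidates the primary management result. It does not. The unadjusted test decides as chi-square does, and in a randomized comparison the arm coefficient on a 0/1 outcome is an adjusted risk difference. Fitted values below zero affect individual prediction, not the arm contrast. Adjustment is also conditional on a baseline difference being found. Nor does the article establish that service use is yes/no; it says only that counselees report their use, which could be a number of visits.

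A reader might also want the primary conclusion to rest on the in-need group alone. With perhaps 33 per arm that is a costly choice. If referral in that group were as low as 5%, at least one arm would have no events in 1 − (1 − 0.95³³)² = 33% of trials.

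**Conclusion.** The point holds as a cheap improvement. The planned all-comer comparison is valid for any referral, but on its own it cannot support a claim of more appropriate management, and it dilutes a gain confined to those with need. Under the assumed rates, untargeted referral alone gives a significant result with probability 0.36 to 0.85 at 25% need and 0.15 to 0.44 at 50%. A targeted rise from 40% to 60% has all-comer power of 0.195 and 0.44 at those two shares, against 0.37 and 0.63 within the in-need group. All referral rates and both need shares are assumptions, so these figures show direction and range, not a forecast.

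The documents do not support saying that a positive result would reflect unneeded referral, only that the planned analysis could not tell. The choice of model is a matter of consistency with negligible effect on the test.

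**What to change.** Under Main research hypotheses, keep the all-comer comparison of referral and add:
- A prespecified report of the arm difference in referral, as a risk difference with 95% confidence interval, separately for counselees with and without need. Define need on the PAHC questionnaire and DT completed before the session: any red domain, a DT score of 4 or more, or a request for support.
- An arm-by-need interaction.
- A rule for the conclusion: claim improved appropriate management only if the increase in referral is not confined to counselees without need.
- For consistency with the analysis of problem prevalence, a binary-outcome method for referral coded yes/no (logistic regression, reported with a risk difference). State how service use is scored before choosing its model.

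The cost is a change of analysis wording; no new data are needed. The by-need intervals will be wide, about ±24 points at 33 per arm, and the interaction will have little power, so the breakdown informs interpretation and does not replace the primary comparison. One caution: this questionnaire is completed after randomization by counselees who are not blinded, so the share with need should be shown by arm.
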